
### Control condition

Participants in the control group will receive the same number of Research Fellow visits and will complete the same questionnaires at the same timepoints as the intervention group. MEMS readings and BP recordings will also be taken, as detailed in the intervention arm. During the first 2 sessions, the Research Fellow will also engage control group participants in non-medication related conversation, e.g. how they are feeling, how they are spending their time etc. in an attempt to provide some control for non-specific effects of attention/social contact.

In both conditions, all interviews will be timed and digitally audio-recorded and transcribed for supervision feedback and check on treatment fidelity.

### Primary outcomes

Medication adherence will be recorded using MEMS (Medication Event Monitoring System, MEMS^® ^Aardex Ltd, Switzerland) pill containers which electronically record openings. Following Brown et al. [17], and in line with previous studies using this method, we shall use the following main outcomes, counting each opening as a presumptive dose: (a) percentage of doses taken (versus doses prescribed), (b) percentage of days on which the correct number of doses was taken, and (c) percentage of doses taken on schedule. Again, following Brown et al. [17], we designate doses as having been taken on schedule if the MEMS bottle was opened within a 3-hour (plus or minus) time window for each dose. The electronic monitoring caps can be connected to a personal computer that reads the data from the pill caps' microprocessors and generates a printout of every pill bottle opening over an extended time period (in this case, the preceding month). Because patients will usually be on a variety of medications, we will target antihypertensive medication for MEMS measurement, particularly as there is clear evidence regarding poorly treated blood pressure significantly increasing the risk of future vascular events, and as stated in the introduction, it is estimated that only 30-50% of patients regularly take their antihypertensive drugs as prescribed [2]. If patients are taking more than one antihypertensive, we shall target the drug that is taken most frequently. MEMS have been successfully used in a variety of medication adherence interventions e.g. Brown et al. [17]. However, as with most methods in this area, MEMS measurement is not immune from the Hawthorne effect, i.e. medication-taking behaviour is often improved in the short-term as a direct consequence of it being measured [26]. We shall therefore use MEMS containers to record medication taking in both intervention and control arms for 3 months. We predict in the control arm that adherence will gradually drop off over the 3 months (as the Hawthorne effect fades), whereas there will be an increase or no change over the 3 months in the intervention arm. A recent three-month RCT aimed at improving adherence to medication in HIV-affected individuals also used this MEMS evaluation of outcome, and in the intention to treat analysis showed no change in the TAU arm, but a significant improvement in the psychological intervention arm, with a controlled effect size of 1.0 [27]. We acknowledge the limitation in this pilot that the Research Fellow will not be blind to treatment arm; however, as our primary outcome is MEMS automated recording of days per month that the correct dose of hypertensive was taken, the potential for bias is significantly reduced.

Secondary outcomes will include (a) MARS self-reported adherence of all secondary preventative medication, (b) systolic and diastolic blood pressure.

### Analysis

MEMS data will be analysed using an intention to treat protocol in a repeated-measures mixed-design (2 groups * 3 time points). One of the primary aims of this pilot study is to determine the effect size achieved by this pilot to inform the sample size calculation for a larger, more definitive multi-centre study. (We acknowledge that the effect size observed may differ from what one would see in a large trial, however, the effect size sought in the large trial should be within the 95% CI of the estimate derived from this pilot. The pilot will thus give a useful measure of the variability of the primary outcome measures). Using G-Power [28] for this pilot, we calculate that with 2 arms of 30 participants, focusing on the treatment group by time interaction term, we should be able to detect an effect size of 0.2, with a power of 0.80 and alpha set at 0.05 (i.e. a 0.2 of a standard deviation improvement in the brief intervention arm in number of days per month that the correct antihypertensive medication is taken, relative to the TAU arm).

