## Methods/Design

### Recruitment

In order to maximise recruitment and the representativeness of the sample, we shall attempt to recruit and obtain consent from consecutive patients who are discharged from the Edinburgh Western General Hospital stroke units and clinics and who are prescribed secondary antihypertensive medication. Our previous experience suggests that this approach will significantly improve trial recruitment. Currently approximately 300 in-patients and 400 out-patients are discharged per year, with over 60% prescribed antihypertensive medication. We will screen 400 first-time stroke (ischaemic and haemorrhagic) or Transient Ischaemic Attack (TIA) patients, and expect a 75% response rate (300). We plan to include both stroke and TIA patients since both groups of patients are treated in a similar way with secondary prevention drugs and are likely to have similar issues with respect to non-adherence [9]. We have decided to focus on the early months following stroke in order to maximise the likelihood of preventing a further stroke. Poor adherence will have a much greater effect on stroke risk in the first few months because the risk of stroke (and thus the absolute risk reductions associated with drug treatment) is highest at this stage [19]. Furthermore, following Petrie et al. [20], we believe that the efficacy of the intervention will be enhanced by eliciting and correcting dysfunctional stroke and medication beliefs soon after preventative drugs are started. However, we have to strike a careful balance between early intervention, and also allowing enough time for participants to demonstrate variance in adherence, so that we can specifically target those showing sub-optimal adherence, thus our decision to assess adherence at 3 months post stroke or TIA. Consenting participants will therefore be contacted by post 3 months after their event and asked to complete the Medication Adherence Self Report Scale (MARS) [21] and return it in a stamped addressed envelope. In this mailing, we will also ask participants to complete the Brief Illness Perceptions Questionnaire [22] and the Beliefs about Medication Questionnaire [23]. This will allow us to economically test the robustness and replicability of the association we previously observed between specific medication concerns and self-reported adherence in a new large sample of TIA/stroke patients. We will then invite all those reporting sub-optimal adherence on the MARS (score of 24 or less) to participate. Based on our earlier study we conservatively estimate that approximately 30% will report some degree of poor adherence, and of those, up to 30% may then decline to participate. We therefore estimate that if we invite 90 patients, 60 will agree to participate. They will then be randomly allocated to brief intervention or treatment as usual (TAU). We are allowing for a further 10% attrition rate during the trial, however, one of the main purposes of this pilot is to obtain data on uptake, acceptability and attrition.

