### Design

A pilot RCT with patients allocated to intervention versus treatment as usual (TAU). Web-based randomisation at the patient level into intervention or TAU will be provided by the Edinburgh Clinical Trials Unit, using minimisation with a random element to ensure that the two trial arms are not significantly different on three key variables: age, number of pills taken per day and baseline MARS adherence. A CONSORT flowchart of the trial design is shown in Figure 1.

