### Control variables

At Session 1, following Trewby et al. [29] and our previous study, all participants will be asked to complete a baseline measure of their perception of the benefit (0-100%) provided by their current stroke prevention medication using a simplified graphical presentation card. Participants will also complete the Mini-Mental State Examination (MMSE), as we previously demonstrated that younger age, lower MMSE and low perceived benefit of medication were all related to poor adherence [15]. Finally, we will determine whether these, and other baseline characteristics (e.g. prior use of reminder packaging and partner involvement in reminding to take medication), are related to treatment outcome.

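### Allocation is minimised on age, pills per day and baseline MARS, but the stated MEMS model includes none of them; if they are prognostic, the arm-difference intervals are too wide

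*Protocol article*

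**What the plan says.** The Design section describes patient-level allocation "using minimisation with a random element" on "three key variables: age, number of pills taken per day and baseline MARS adherence". The Analysis section gives the primary model in one sentence, "MEMS data will be analysed using an intention to treat protocol in a repeated-measures mixed-design (2 groups * 3 time points", and names no covariate. Its power statement is made "with 2 arms of 30 participants, focusing on the treatment group by time interaction term". The same section says that the pilot's effect size, its 95% confidence interval and the variability of the primary outcomes will inform the sample size of the larger trial.

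The Control variables section mentions age, MMSE and perceived benefit, and asks whether these and other baseline characteristics "are related to treatment outcome". It does not place them in the treatment comparison.

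Under Intervention, MEMS bottles are first filled at the end of session 2, so no MEMS value precedes the intervention. MARS is collected by post at screening, and only patients scoring 24 or less are invited.

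**The concern.** Minimisation makes the arms more alike on its factors than simple randomisation would. If those factors predict the outcome, the true sampling variation of the arm difference is smaller than an unadjusted analysis assumes, because their variance stays in the error term. The test is then conservative and the interval too wide.

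Prognostic value is plausible from the article. Younger age was related to poor adherence in the team's earlier study. Having too many tablets is listed among the concerns that drove poor adherence. Baseline MARS is itself a measure of adherence, and the only one taken before the intervention.

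The arm difference matters even though power was set on the interaction. MEMS recording starts only after both intervention sessions, so a benefit already present in month 1 shows as a difference in level, not as a difference in trend. Research questions (b) and (d), on whether adherence improves and what effect size is seen, depend on that level. So does the interval passed to the larger trial.

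**Working it through.** **The plan's own figure.** The article states "we should be able to detect an effect size of 0.2, with a power of 0.80 and alpha set at 0.05", explained as "a 0.2 of a standard deviation improvement in the brief intervention arm". For the interaction with N = 60, m = 3 and f = 0.2, the noncentrality is λ = f²·N·m/(1−ρ), with 2 and 116 degrees of freedom. Power is 0.66 at ρ = 0, 0.82 at ρ = 0.3 and 0.93 at ρ = 0.5. It equals 0.80 only at ρ of about 0.27, and no ρ is stated. Read literally as 0.2 SD between two arms of 30, two-sided power is 0.12. That is a separate problem, and nothing below depends on it.

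**Inputs.** From the article: 30 per arm, three monthly MEMS values, three minimisation factors, and 10% attrition ("We are allowing for a further 10% attrition rate during the trial"), which leaves 27 per arm. Assumed: R², the share of a single month's MEMS variance explained by the three factors, from 0 to 0.33; correlation between months ρ = 0.5; covariate effects constant over time. Results are in units of the single-month SD.

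**Three-month mean difference, 30 per arm.**
- Variance of a patient's mean: (1 + 2ρ)/3 = (1 + 1)/3 = 0.667.
- Unadjusted half-width: t(58)·√(0.667 × 2/30) = 2.002 × 0.211 = 0.42.
- Adjusted half-width, near-balanced arms: t(55)·√((0.667 − R²) × 2/30), with t(55) = 2.004.

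| R² | Adjusted half-width | Unadjusted type I error (simulated) |
|---|---|---|
| 0.10 | 2.004 × √(0.567 × 0.0667) = 0.39 | 0.039 to 0.040 |
| 0.20 | 2.004 × √(0.467 × 0.0667) = 0.35 | 0.030 to 0.031 |
| 0.33 | 2.004 × √(0.337 × 0.0667) = 0.30 | 0.014 to 0.021 |

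The type I errors come from simulated minimised trials with no true effect (30 + 30, ρ = 0.5, assignment probability 0.8). The ranges are across repeat simulations. The adjusted analysis stayed at about 0.05. The simulated half-widths agree with the table to within 0.01. At R² = 0 the adjusted interval is about 1% wider, from the lost degrees of freedom and residual imbalance.

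**Single-month difference.** Half-width = t·√((1 − R²)·(2/n)·(1 + 3/(2n − 6))), against t·√(2/n) unadjusted.
- n = 30: 0.517 unadjusted; 0.532, 0.518, 0.504, 0.475 and 0.435 adjusted at R² = 0, 0.05, 0.10, 0.20 and 0.33. The gain is 2.5% at 0.10, 8% at 0.20 and 16% at 0.33. Break-even is R² of about 0.055.
- n = 27: 0.546 unadjusted; 0.535, 0.504 and 0.461 at R² = 0.10, 0.20 and 0.33.

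The factor 1 + 3/(2n − 6) allows for the imbalance expected under simple randomisation. Minimisation reduces that imbalance, so the break-even is if anything lower.

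**Group by time (month 3 minus month 1).** A fixed baseline value with a constant effect cancels from a within-patient change. The variance of the change is 2(1 − ρ) = 1 whatever R² is, so the half-width is 2.002 × √(2/30) = 0.517. Simulation gives 0.513 to 0.515 unadjusted and 0.519 to 0.52 adjusted, with type I error near 0.05 either way.

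**The case against.** The strongest objection is that this argues from silence. The article names a design in one sentence, does not exclude covariates, and a covariate list is often left to an analysis plan, which is not shown. A reader might infer that the protocol has decided against adjustment; the text does not go that far. What remains is that the model as written does not reflect the allocation method, and that the section headed Control variables does something other than adjust.

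The second objection is that the powered contrast is the interaction. That stands: a reader might infer that every interval is too wide, but the interaction interval is not, unless covariate effects change over time.

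The third is that the size is assumed. That also stands. The earlier study's one-third of variance explained might be read as evidence of a large gain. It concerns self-reported adherence and four variables, of which only age is a minimisation factor. MARS is cut off at 24 in this sample and is described as prone to ceiling effects, so it may predict weakly. Converting R² into an effective sample size of 60/(1 − R²) ignores the cost of fitting three covariates and does not apply to the interaction.

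Three further readings are not supported. Baseline MARS does not go unused: it screens patients, drives allocation, and is the baseline of a secondary outcome. The raw SD is not a wrong planning input; it is legitimate and cautious. No blood pressure model is stated, so none can be called wrong.

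**Conclusion.** The point holds for the monthly and overall arm differences in MEMS adherence, on the condition that the minimisation factors are prognostic. The stated analysis is then conservative. At assumed R² between 0.10 and 0.33, the half-width for the three-month mean is about 0.03 to 0.12 SD larger than it need be (0.42 − 0.39 to 0.42 − 0.30). At R² near zero, adjustment slightly widens it. These figures rest on an assumed R², ρ = 0.5 and effects constant over time, none of which the article supplies. The error is in the cautious direction and does not inflate false positives. It still affects the estimate and interval that the pilot exists to provide, and naming the covariates is a better method than the one stated.

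**What to change.** In the Analysis section:
- Include age, number of pills per day and baseline MARS, each as a continuous covariate, in the MEMS model.
- Report the adjusted overall and monthly arm differences with 95% confidence intervals alongside the group-by-time test.
- Report both the raw SD and the adjusted residual SD, so that the larger trial can plan on either.
- Adjust the MARS secondary outcome for baseline MARS, and blood pressure for baseline blood pressure.

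This is a few lines of text. Age, baseline MARS and baseline blood pressure are already collected, and the pill count is needed for minimisation. The cost is three degrees of freedom in the MEMS model and a slightly wider interval if the factors turn out not to be prognostic.

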### Research questions

(a) Is the brief intervention feasible, understandable and acceptable (e.g. regarding uptake/attrition)?

(b) Does the intervention improve adherence?

(c) Is improvement in adherence mediated by (i) changes in illness and medication beliefs and/or (ii) reduced forgetting?

(d) What effect size is observed to inform the power calculation for a larger, more definitive study?

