### Timetable

This is a 31-month project. The Research Fellow will spend months 1-3 learning techniques for eliciting and modifying patients' dysfunctional beliefs regarding their stroke and their medication. Patients will be invited to participate from month 3 onwards. It is anticipated that the running of the trial will take 24 months (months 4-27). Postal recruitment will be used to collect baseline data on the MARS, BMQ and BIPQ self-report measures, and to identify participants who are suitable for the intervention. Each participant recruited into the intervention will participate for roughly four months, thus we envisage 6*4 month blocks, with approximately 10 patients being run concurrently in any one of these blocks. They will each require 5 face-to-face contacts (choice of home visit or meeting in the local Clinical Research Facility) over the participation period. Session 1 is when the remaining baseline measures will be completed and the implementation worksheet plan drawn up. Session 2 is two weeks later when the plan is reviewed and elicitation and modification of illness and medication beliefs will be conducted, and the MEMS containers filled for the following month. Sessions 3 and 4 are brief monthly meetings to take a MEMS cap reading and refill the MEMS bottle. BMQ and BIPQ scores will also be collected at Session 3. The final outcome measures will be taken at Session 5. Months 28-31 will be spent analysing the data and in preparing the final report and papers for conference presentation and publication.

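### The only term the plan names and powers, group by time, cannot register a benefit already present in month 1, because all three MEMS time points follow the intervention

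*Protocol article*

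**What the plan says.** All references are to the protocol article.

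- **Model (Analysis).** "MEMS data will be analysed using an intention to treat protocol in a repeated-measures mixed-design (2 groups * 3 time points").
- **Powered term (Analysis).** The sample-size sentence works "with 2 arms of 30 participants", "focusing on the treatment group by time interaction term", and concludes: "we should be able to detect an effect size of 0.2, with a power of 0.80 and alpha set at 0.05". It then explains this effect as "a 0.2 of a standard deviation improvement in the brief intervention arm" relative to treatment as usual (TAU), counted in days per month with correct dosing.
- **Timing (Intervention; Timetable).** The if-then plan is drawn up in Session 1. Two weeks later, Session 2 reviews the plan, addresses beliefs, and ends with "the MEMS containers filled for the following month". The caps are read at Sessions 3, 4 and 5.
- **Reason for expecting an interaction (Primary outcomes).** "We predict in the control arm that adherence will gradually drop off over the 3 months (as the Hawthorne effect fades"), while the intervention arm is expected to rise or stay level.
- **What the pilot must answer (Research questions).** Question (b) is "Does the intervention improve adherence"; question (d) asks for the effect size on which to power the larger trial.

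**The concern.** In a design with a pre-treatment measurement, the group-by-time interaction carries the treatment effect, because the arms should be equal at the first point and can differ later. Here the first point is already one month after the complete intervention. The interaction therefore asks only whether the difference between arms changes from month to month. Any difference open in month 1 and still there in month 3 drops out of the test.

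Two things are at stake. First, the pilot could show a large, steady advantage and yet have a null result on its powered test, or show a significant result because an early advantage disappeared. Second, an effect size taken from the interaction would describe divergence between months, whereas questions (b) and (d) call for the difference in adherence between arms.

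**Working it through.** **Inputs from the article.** 30 per arm (N = 60); m = 3 time points; alpha 0.05; stated effect 0.2; stated power 0.80; 10% attrition, hence 27 per arm (30 x 0.9).

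**Assumed, because not stated.** Normal outcomes with SD 1 and equal correlation rho between months, varied over 0.3, 0.5 and 0.7.

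**1. The plan's own figure.** For a within-between interaction with effect size f, the noncentrality is f² N m / (1 - rho) = 0.04 x 60 x 3 / (1 - rho) = 7.2 / (1 - rho), on 2 and 116 df. Power is 0.66 at rho = 0, 0.79 at 0.25, 0.80 at 0.27, 0.82 at 0.30, 0.93 at 0.5 and 0.99 at 0.7. The stated 0.80 is thus reached on this formula if 0.2 is Cohen's f and rho is about 0.27. It is not the power for a 0.2 SD difference between arms: one two-sample comparison with d = 0.2 and 30 per arm has power 0.12 and would need 393 per arm.

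**2. What the interaction sees.** Let D1, D2, D3 be the true gaps between arms in months 1 to 3 and Dbar their mean. With n per arm,

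- interaction noncentrality = (n/2) x Σ(Dj - Dbar)² / (1 - rho);
- group effect on the three-month mean: Dbar / √[((1 + 2 rho)/3) x (2/n)];
- linear contrast: (D3 - D1) / √[2(1 - rho) x (2/n)].

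If D1 = D2 = D3, the first expression is zero whatever their size, so power equals alpha.

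**3. Numbers, n = 27, rho = 0.5.**

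| Gap in months 1, 2, 3 (SD) | Interaction (2 df) | Linear contrast (1 df) | Group effect |
|---|---|---|---|
| 0.7, 0.7, 0.7 | 0.05 | 0.05 | 0.87 |
| 0.3, 0.5, 0.7 | 0.235 | 0.30 | 0.60 |
| 0, 0.35, 0.7 | 0.62 | 0.71 | 0.34 |
| 0.8, 0.4, 0 | 0.74 | 0.82 | 0.42 |

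Worked example, third row: Σ(Dj - Dbar)² = 0.35² + 0 + 0.35² = 0.245, and the noncentrality is 13.5 x 0.245 / 0.5 = 6.615, giving 0.62 on 2 and 104 df.

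Simulation (20,000 runs per scenario, 30 per arm, rho 0.3, 0.5 and 0.7) agrees: constant benefits of 0.2, 0.5, 0.8 and 1.0 SD gave interaction rejection rates of 4.6% to 5.0%.

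**4. What 30 per arm can detect as a level difference.** (1.96 + 0.8416) x √(2/30) = 0.723 SD for a single month. Averaging three months multiplies this by √((1 + 2 rho)/3):

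- rho 0.3: 0.723 x 0.730 = 0.53 SD
- rho 0.5: 0.723 x 0.816 = 0.59 SD
- rho 0.7: 0.723 x 0.894 = 0.65 SD

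For a constant 0.2 SD difference the power is 0.18, 0.15 and 0.14 respectively.

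**The case against.** The choice of the interaction is reasoned. The authors expect monitoring itself to lift adherence at first and the lift to fade in the control arm only. That is a group-by-time hypothesis. If the arms do start equal, the interaction is the better test: 0.62 against 0.34 in the third row of the table. This stands, but the article nowhere says that the arms will be equal in month 1, and the test captures the whole benefit only if they are.

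The immediate, constant benefit is an assumption of this review. The epilepsy study is cited with overall percentages and no monthly course, so it shows neither a constant nor a widening gap. This also stands. The profile is still plausible, since the Background describes if-then plans as acting promptly and the plan is in place two weeks before recording begins.

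A reader might infer that the trial cannot answer question (b), or that its analysis rests wholly on the interaction. The article does not support that. The phrase about the interaction belongs to the sample-size sentence, the 2 x 3 model also yields a group effect, and nothing rules out reporting it. Nor does the article say which estimate will be carried to the larger trial.

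**Conclusion.** The point holds in limited form. All three MEMS points follow the full intervention, and the only term named and powered is blind to any gap that is constant from month 1. That part is algebra and does not depend on the assumed correlation. A significant interaction does not by itself show benefit either, since a fading effect can produce one. The Analysis section also disagrees with itself: it powers an interaction and describes the result as a 0.2 SD difference in level relative to TAU. Questions (b) and (d) need the level difference.

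The benefit is invisible to the named and powered test, not to the data. For a pilot whose first question is feasibility, this should be fixed before analysis but does not undermine the design. The power figures rest on normal outcomes, equal correlations and the gap profiles shown.

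**What to change.** 1. Name the between-arm difference in mean MEMS adherence over the three months, with its 95% CI, as the primary estimate and as the effect size carried to the definitive trial. Obtain it from the same repeated-measures model, adjusted for baseline MARS (the only adherence measure taken before randomisation) and the other minimisation factors, age and number of pills per day.
2. Keep the predicted divergence as a secondary 1-df group-by-linear-month contrast, and report the difference at each month.
3. Restate the power sentence for the new contrast: about 0.53 to 0.65 SD at 80% power with 30 per arm, unadjusted, for assumed correlations of 0.3 to 0.7. State the effect metric and the correlation used.

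Cost: no new data or visits, but the sample-size statement must be redone as well as the analysis wording. The downside is lower power if the arms start equal and only diverge: about 34% for the mean difference against 62% for the omnibus interaction, for a gap rising from 0 to 0.7 SD with 27 per arm and correlation 0.5. The secondary linear contrast, at about 71%, covers that case.

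### The stated 80% power does not hold for a 0.2 SD improvement on the group-by-time interaction; with 30 per arm, power for that effect is about 8% to 13% at between-month correlations of 0.3 to 0.7

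*Protocol article*

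**What the plan says.** The Analysis section plans a mixed repeated-measures analysis of the electronic adherence data, with two groups and three monthly time points. The power statement opens with "Using G-Power [28] for this pilot, we calculate" and continues, for two arms of 30, with "focusing on the treatment group by time interaction term, we should be able to detect an effect size of 0.2", at power 0.80 and alpha 0.05. The sentence then gives its own meaning for that number: "i.e. a 0.2 of a standard deviation improvement in the brief intervention arm", counted in monthly days on which the correct antihypertensive dose is taken, compared with treatment as usual.

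The section does not say which effect-size index the 0.2 is. It also does not give the correlation between months or a sphericity correction.

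Two other places bear on the point. Under Primary outcomes, the authors predict a gradual fall in adherence in the control arm over the three months, against an increase or no change in the intervention arm. Under Recruitment, they allow for a further 10% attrition.

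**The concern.** An interaction test in a 2 × 3 design responds to how much the gap between the arms changes over the months. Its usual standardised effect size in G*Power is Cohen's f, which is the spread of the interaction cell effects relative to the SD. That is not a difference between two means in SD units. The power sentence names the interaction and the software, then describes 0.2 as a mean difference in SDs.

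If the two have been confused, the sentence credits 60 patients with detecting a very small benefit when they can detect only a large one. This sentence is the plan's only quantitative account of what the sample can show. Research question (b) asks whether adherence improves, and question (d) asks for an effect size to plan the larger study, so the scale on which effects are expressed needs to be right.

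**Working it through.** **Inputs from the protocol article (Analysis).** N = 60 (30 per arm), k = 2 groups, m = 3 months, alpha 0.05, stated power 0.80, effect size 0.2.

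**Assumptions, because the document gives no value.** Correlation ρ between months from 0 to 0.9, equal for all pairs of months; sphericity (ε = 1).

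**Test.** The within-between interaction F test has df1 = (k−1)(m−1) = 2 and df2 = (N−k)(m−1) = 116. Its noncentrality is λ = f²·N·m/(1−ρ) = 180·f²/(1−ρ). For 80% power at alpha 0.05, λ must be about 9.89.

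**Step 1: reproduce the stated 80%.** Take 0.2 as Cohen's f, so λ = 180 × 0.04/(1−ρ) = 7.2/(1−ρ).

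| ρ | 0 | 0.25 | 0.3 | 0.5 |
|---|---|---|---|---|
| Power at f = 0.2 | 66% | 79% | 82% | 93% |

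Setting 7.2/(1−ρ) = 9.89 gives ρ ≈ 0.27. The stated figure is therefore recovered under the f reading with that one correlation. With 54 analysed (10% attrition), the same power needs ρ ≈ 0.35.

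**Step 2: convert between SD units and f.** Let the gap between the arms in each month be in SD units. Then f is the root mean square, over the three months, of half the centred gaps.
- Linear widening, gaps 0, D/2, D: f = √[(D²/16 + 0 + D²/16)/3] = D/√24.
- Step, gaps 0, 0, D or 0, D, D: f = D/√18. This is the most favourable pattern for a given D.
- Constant gap, D in every month: f = 0.

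**Step 3: power for 0.2 SD as the sentence defines it.** For linear widening, f = 0.2/√24 = 0.041 and λ = 0.3/(1−ρ). For a step, f = 0.2/√18 = 0.047 and λ = 0.4/(1−ρ).

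| ρ | 0 | 0.3 | 0.5 | 0.7 | 0.8 | 0.9 |
|---|---|---|---|---|---|---|
| Linear | 7% | 8% | 10% | 13% | 17.5% | 31% |
| Step | 8% | 9% | 11% | 16% | 22% | 41% |

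Reaching λ = 9.89 needs 1−ρ = 0.3/9.89 = 0.030 (ρ ≈ 0.97) for linear widening, or 0.4/9.89 = 0.040 (ρ ≈ 0.96) for a step. A constant 0.2 SD gap gives no interaction, so power equals alpha, 5%. As a cross-check outside the interaction, a two-sided two-sample t test at a single month has 12% power for 0.2 SD.

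**Step 4: what f = 0.2 means in SD units.** Linear: D = 0.2 × √24 = 0.98 SD. Step: D = 0.2 × √18 = 0.85 SD. Relative to 0.2 SD these are factors of 4.9 and 4.2.

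**Step 5: what the design detects at 80% power.** The linear widening is D = √24 × √[λ(1−ρ)/(3N)], with λ = 9.89 for 60 analysed and 9.92 for 54.

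| ρ | 0.3 | 0.5 | 0.7 |
|---|---|---|---|
| 60 analysed | 0.96 SD | 0.81 SD | 0.63 SD |
| 54 analysed | 1.01 SD | 0.86 SD | 0.66 SD |

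**The case against.** **The index is not named.** The text says only that an effect size of 0.2 is detectable, so Cohen's f is inferred from the software and the test. The match to 80% also depends on choosing a free correlation of 0.27. This stands, and the f reading should be offered as the likely explanation, not as fact. The error does not rest on it: taken literally in SD units, the sentence fails at every correlation up to 0.9.

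**The correlation is unknown.** This also stands, and it is why a range is shown. A reader might infer an absolute floor, such as nothing below about 0.6 SD being detectable. The documents do not support one: at a correlation of 0.9 the interaction would detect about 0.36 SD (linear) or 0.31 SD (step).

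**It is a pilot.** Low power is no fault in a pilot, and the Analysis section says planning will draw on the confidence interval of the observed effect and on the outcome's variability. A reader might infer that the definitive trial's sample size will be wrong, or that a null result will be taken to exclude 0.2 SD. The document plans neither use of the detectable effect. What remains is a false statement of what 60 patients can show.

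**The contrast could be changed.** A reader might infer that the interaction should give way to a comparison of three-month means. Nothing in this defect requires that: the interaction fits the authors' prediction that the arms drift apart.

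**Conclusion.** The power statement is wrong as written. The claimed 80% becomes 8% to 13% for a linear 0.2 SD divergence at correlations of 0.3 to 0.7, and at most 41% under the most favourable pattern at a correlation of 0.9. These figures assume 60 patients analysed, sphericity and equal correlation between months.

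The most likely cause is that an interaction effect size f = 0.2 was described as a mean difference in SDs. If so, the detectable divergence is understated four- to five-fold. The mis-statement is established; its cause is inferred. The sample size and the choice of the interaction test are not faulted.

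**What to change.** In the Analysis section, delete the explanation of 0.2 as a fraction of a standard deviation. Name the effect-size index that was entered, state the assumed between-month correlation and any sphericity correction, and give the detectable interaction in SD units.

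Possible wording, if the index was Cohen's f: *With 30 patients per arm and alpha 0.05, the group-by-time interaction test has 80% power for a linear widening of the between-arm gap from month 1 to month 3 of about 0.96, 0.81 or 0.63 SD at between-month correlations of 0.3, 0.5 or 0.7. After 10% attrition the corresponding values are about 1.01, 0.86 and 0.66 SD.*

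The authors should confirm the index and correlation from their own calculation record. The cost is one reworded sentence and a less favourable stated figure, with no extra patients and no change to the powered contrast.
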